| Take photos of injection site reactions                                               |                               |         |                 |                       |                             | (X)     |         | (X)     |         | X                      | (X)      |          |          |          |
| Issue and collect Diary                                                                |                               | X       |                 |                       | X                           | X       | X       | X       | X       |                        | X        |          | X        |          |
| Review diary cards for compliance and adverse events.                                              |                               |         | X               | X                     | X                           | X       |         | X       |         | X                      | X        | X        | X        |          |
| Optional skin biopsy                                                                               |                               |         |                 |                       |                             |         |         |         |         | X                      |          |          |          |          |
| Patient education regarding swab collection, diary completion and outbreak management  |                               | X       | X  | X        |                             |         |         |         |         |                        | X        | X        |          |          |
| Adverse Event and Outbreak assessment                                                              |                               | X       | X               | X                     | X                           | X       | X       | X       | X       | X                      | X        | X        | X        | X        |
| Concurrent Medications                                                                             | X                             | X       | X               | X                     | X                           | X       | X       | X       | X       | X                      | X        | X        | X        | X        |

Table 1 Table of Assessments 2 –Study Period 2 to Follow up

| Assessments                                                                                        | Study Period 2  |          |          |          |          | Follow up  |          |                   |
|----------------------------------------------------------------------------------------------------|-----------------------------|----------|----------|----------|----------|------------------------|----------|-------------------|
|                                                                                                    | Visit 15                    | Visit 16 | Visit 17 | Visit 18 | Visit 19 | Visit 20               | Visit 21 | Visit 22          |
|                                                                                                    | W23                         | W24      | W25      | W28      | W31      | W36                    | W42      | End of Study/ W48 |
| Informed consent                                                                                   |                             |          |          |          |          |                        |          |                   |
| Review inclusion/exclusion criteria                                                                |                             |          |          |          |          |                        |          |                   |
| Demographics, Medical/Surgical History                                                             |                             |          |          |          |          |                        |          |                   |
| Physical Examination (symptom directed)                                                            | (X)                         | (X)      | (X)      | (X)      | (X)      |                        |          | (X)               |
| Vital signs/Body Weight/Height                                                |                             | X        |          | X        |          |                        |          | X                 |
| Electrocardiogram                                                                      |                             |          |          |          |          |                        |          |                   |
| Urine Pregnancy Test                                                                   |                             | X        |          |          |          |                        |          | X                 |
| Haematology                                                                            | X                           | X        | X        | X        |          |                        |          | X                 |
| Chemistry                                                                              | X                           | X        | X        | X        |          |                        |          | X                 |
| Coagulation                                                                                        |                             |          |          |          |          |                        |          |                   |
| Urinalysis                                                                             |                             | X        |          |          |          |                        |          | X                 |
| Viral Serology (HIV, Hepatitis B and C, HSV-1 and 2)                                               |                             |          |          |          |          |                        |          |                   |
| ELISA (antibody)                                                                                   |                             | X        |          | X        |          |                        |          | X                 |
| ELIspot (T cell)                                                                                   |                             | X        | X        |          |          |                        |          | X                 |
| Exploratory Immune assays (T cell and/or genetic testing)                             |                             | X        | X        |          |          |                        |          | X                 |
| Randomisation                                                                                      |                             |          |          |          |          |                        |          |                   |
| Phone call                                                                                         |                             |          |          |          |          | X                      | X        |                   |
| Study vaccine administration and bleb check/measurement                                            |                             | X        |          |          |          |                        |          |                   |
| Collection of daily swabs from mucocutaneous genital sites for viral shedding for 45 days          |                             |          | X        |          |          |                        |          |                   |
| Take photos of injection site (s)                                                     |                             |          | X        |          |          |                        |          |                   |
| Issue and collect Diary                                                                |                             | X        | X        |          | X        |                        |          |                   |
| Review diary cards for compliance and adverse events.                                              |                             |          | X        | X        | X        |                        |          |                   |
| Skin biopsy                                                                                        |                             |          |          |          |          |                        |          |                   |
| Patient education regarding swab collection, diary completion and outbreak management  |                             |          | X        | X        |          |                        |          |                   |
| Adverse Event and Outbreak assessment                                                              | X                           | X        | X        | X        | X        | X                      | X        | X                 |
| Concurrent Medications                                                                             | X                           | X        | X        | X        | X        | X                      | X        | X                 |

 Height and weight to be performed at Visit 1 only

 Vital signs include resting BP, heart rate, respiratory rate and temperature

 Safety assessments to be performed prior to investigational vaccine/placebo.

 Vital signs to be performed prior to investigational vaccine/placebo administration at 30 minutes and 60 minutes following each dose.

 Urine pregnancy testing will be conducted in female participants at Screening, before each administration of study vaccine and at the end of study visit. If positive, a serum pregnancy will be conducted and the vaccine will not be administered.

|               |                                                                                                                                                                                                                                                                      |
|---------------|----------------------------------------------------------------------------------------------------------------------------------------------------------------------------------------------------------------------------------------------------------------------|
|   | To be repeated as deemed necessary by site staff                                                                                                                                                                                                                     |
|   | Subject to document daily whether any HSV-2 symptoms have occurred during the shedding assessments. Following receiving the investigational vaccine/placebo, the subject to document the existence and nature of any injection site reactions that occur for 7 days. |
|   | Visit window is +/- 3 days                                                                                                                                                                                                                                           |
|   | Visit window is +/- 5 days                                                                                                                                                                                                                                           |
|  | Subjects to be either contacted via phone or visit clinic to assess swabbing technique. If subject has had difficulties in collecting swabs since Visit 2, the subject is to be re-educated.                                                                         |
|  | Visit 10 has a visit window of +/- 12 hours                                                                                                                                                                                                                          |
|  | Site to take a photo of any injection site(s)                                                                                                                                                                                                                        |
|  | Optional phone visit for subjects that require additional support with the Baseline Swabbing Assessment                                                                                                                                                              |
|  | Genetic exploratory testing will only be performed in subjects who provide written informed consent. Genetic exploratory analysis may include HLA typing and T-cell receptor typing.                                                                                 |
|  | Visit window is +/- 7 days                                                                                                                                                                                                                                           |

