| Study procedures:  | 
Please refer to Table 1.
 
Screening/ Run in:
 
Subjects who provide voluntary written informed consent will be screened for preliminary eligibility. At screening, subjects will also be invited to provide written informed consent for the optional skin biopsy that will be collected at Visit 10.
 
Preliminarily eligible subjects will commence collecting once daily swabs of genital secretions for HSV-2 testing for 45 days from Visit 2. During this and each subsequent swabbing period,
                                                                                                                                                                                                                                                                                                                                                                                  |

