|  | 
subjects will be given diaries and asked to collect daily information about swab collection and HSV-2 symptoms that they may experience.
 
Two days after the commencement of the Baseline shedding assessment period, subjects will be contacted via telephone by the Investigator or designee to discuss the subject's progress and compliance with daily swab collection. If there are any doubts about the quality of the swabbing or compliance, the subject will be encouraged to attend an unscheduled clinic visit so that further education can be provided. A week after the patient commenced the Baseline Shedding Assessment (Visit 4) the site may contact the subject via telephone again to check compliance and address any logistical issues with shipment of swabs to the designated virology laboratory. Visit 4 is optional and dependant on the subject's requirements, as assessed by the Investigator or designee.
 
The site will be encouraged to keep regular phone contact with the subject during the Run-in shedding assessment to ensure that the subject can comply with this requirement. Unscheduled clinic visits may also be arranged for this purpose.
 
Should a subject develop genital lesions during the Baseline shedding assessment they will be instructed to contact the clinic. An additional set of swabs will be collected for PCR or viral culture.
 
Study Period 1 (Treatment Period):
 
At Baseline (Day 0), subject eligibility will be confirmed. Subjects meeting all inclusion and no exclusion criteria will be randomised to receive either the investigational vaccine or placebo will be in a 3:1 ratio. In total, the subjects will receive 3 doses of investigational vaccine or placebo at 4 weekly intervals (Day 0, Week 4, and Week 8). The subject will keep a diary and record any injection site reactions each day for 7 days after receiving the injection(s). Subjects will return to the clinic one week after each administration of investigational vaccine/placebo for immune monitoring at Week 1, 5 and 9 (Visits 6, 8 and 11).
 
In addition, subjects will return to the clinic 48 hours (Visit 10) after their third dose of investigational vaccine/placebo received at Week 8. The Investigator will assess the subject's injection site(s). The Investigator or designee will take a photo using a standardized approach. Additionally, all subjects who provide written informed consent for the skin biopsy at screening will have the tissue collected from the injection site region regardless of whether they have had a visible injection site reaction. Please see Section 6.4.11 of the protocol.
 
One week after the third vaccination (Week 9), subjects will commence collecting post-treatment swabs for viral culture for 45 days. Subjects will return at Week 12 (Visit 12) for immune monitoring and safety assessments and at Week 15 (Visit 13) having completed the 45 days swab collection.
 
At Week 19, subjects will be contacted by phone and adverse
 |

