|                                             | 
event/concurrent medication questioning will occur
 
Study Period 2 (Booster Injection):
 
At Week 23 (Visit 15), one week prior to the booster vaccination/placebo administration, the subject will attend the clinic and safety assessments will be performed.
 
At Week 24 (Visit 16), subjects will be administered a single booster vaccination/placebo.
 
At Week 25 (Visit 17), immune monitoring will be performed. Subjects will also be required to collect genital swabs for viral culture for 45 days from Week 25. Swabs will be sent to the laboratory for viral load testing, virus typing and/or sequencing.
 
At Week 28 (Visit 18), immune monitoring and safety assessments will again be performed.
 
Follow up:
 
Subjects will be contacted via the telephone at Week 36 and 42 (Visits 20 and 21). Adverse event and concurrent medications will be recorded.
 
End of Study:
 
At Week 48 (Visit 22), safety assessments will be performed.
 
Additional information:
 
Subjects will be required to suspend all HSV-2 medication during the shedding assessments and for one week prior to the Run-in shedding assessment and throughout the study period.
 
Urine pregnancy testing will be conducted for female subjects at Screening, before administration of each dose of investigational vaccine/placebo and at the End of Study Visit. If positive, a serum pregnancy test will be conducted and the study investigational vaccine/placebo will not be administered until the result of this is received. If the result of the serum pregnancy test is negative, administration of investigational vaccine /placebo will continue. If the result of the pregnancy test is positive, the subject will be withdrawn from the study.
 
Vital signs will be recorded prior to study vaccine/placebo administration and at 30 minutes and 60 minutes following each dose. Subjects will be required to remain in the clinic for at least 60 minutes after administration or longer if clinically indicated.
 
Blood samples will be collected and shipped to nominated laboratories for preparation of serum and peripheral blood mononuclear cells (PBMCs) for use in immunological analyses (T-cell and antibody responses).
 |

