| Clinical procedures / assessments:     | Refer to Tables 1 & 2                                                                                                                                                                                                                                                                                                                                                                                                                                                                                                                                                                                                                                                                                                                                                                                                                                                                                                                                                                          |
| Specialised analyses:                  | 
 
• T-cell responses to HSV-2 gD2 will be primarily assessed by interferon gamma Enzyme-Linked Immunosorbent Spot assay (ELISPOT) at specified time points during the study period.
 
• Antibody responses against HSV-2 gD2 will be monitored using ELISA.
 
• PCR analysis for presence and quantification of viral shedding and type.
 
• Other exploratory immunological assays may be performed such as the monitoring of both T-cell responses (e.g. using intracellular cytokine staining, FACS and MHC tetramer analysis), T-cell receptor and HLA typing and humoral immune responses against HSV-2 antigens (e.g. using ELISA based methodologies).
 
                                                                                                                                                                                                                                                             |

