### 5.2 Inclusion Criteria

The criteria for entry into the study are:

1. Diagnosis of genital HSV-2 infection confirmed by positive HSV-2 serology or if negative a documented positive HSV-2 pathology result, AND positive PCR for HSV-2 during the Baseline Shedding Assessment prior to randomisation
2. A history of recurrent genital HSV-2 for at least 12 months AND a self-reported history of at least 3 and no more than 9 reported lesion occurrences in the 12 months prior to Screening or, if currently on suppressive therapy, in the 12 months prior to initiation of suppressive therapy.
3. Aged 18 to 50 years, inclusive.
4. Male or female. Women of child-bearing potential must be using two effective methods of contraception and agree to continue to do so from Screening, throughout Investigational vaccine/placebo dosing and for 28 days after the last dose of investigational vaccine/placebo.
5. Has voluntarily given written informed consent.

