### **6.3.2 Study Period 1 (Treatment period)**

#### **6.3.2.1 Visit 5/Day 0/Baseline**

On Day 0 prior to vaccine administration, the following assessments will be performed and documented:

- Review of Inclusion/exclusion criteria paying particular attention to compliance with the Run-in swabbing requirements and whether HSV-1 was identified by PCR during the Run-in shedding assessment (see Section 5.2 and 5.3);
- Urine samples for urinalysis and pregnancy testing (see Section 6.4.5 and 6.4.6);
- A symptom directed physical examination (see Section 6.4.2);
- Vital signs(see Section 6.4.3);
- Concurrent medication assessment (see Section 7);
- Adverse event questioning (see Section 8);
- Blood samples for:
  - Haematology (see Section 6.4.5);
  - Clinical chemistry (see Section 6.4.5);
- Blood samples for immunological assessments including:
  - ELIspot (T cell responses specific for HSV-2 gD2) (see Section 6.4.5);
  - ELISA (anti HSV-2 gD2 antibodies) (see Section 6.4.5);
  - Exploratory Immune assays (see Section 6.4.5); and
- Review of HSV-2 Symptoms and Swabbing Diary (see Section 6.4.10).

Once the above assessments have been performed, the patient will be randomised. The vaccination/placebo will be administered and the resultant bleb will be inspected and measured in mm. The results of the bleb inspection will be recorded in the source documents.

Vital signs will be measured at 30 and 60 minutes following the administration of the investigational vaccine/placebo. Subjects will be observed during this time.

Adverse event and concomitant medication questioning will occur.

The subject will be issued with an Injection Site Reaction Diary and instructed to view their injection site(s) at the same time each day and record their findings every day for 7 days.

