#### **6.4.9 Genital viral shedding assessments**

Subjects will be educated regarding genital swab collection, diary booklet completion and HSV-2 outbreak management. The requirement for compliance in these aspects of the study should be reinforced as often as possible. Additional unscheduled visits may be scheduled for educational purposes should the Investigator or designee judge that this is required.

Daily genital swabs to detect viral shedding will be performed for 45 days commencing as follows:

1. Run-in Shedding Assessment - prior to the first vaccination.
2. Post Vaccination Shedding Assessment - commencing one week following the third investigational vaccine/placebo (Study Period 1); and
3. Post Booster Shedding Assessment - commencing one week after the booster vaccination/placebo (Study Period 2).

Prior to commencing the first assessment period, each subject will be given written gender specific instructions for obtaining genital swabs.

The subject will be instructed to take the swabs at the approximately the same time of the day. Ideally this will be before bathing.

If the subject does not collect a swab at the planned time they will be instructed to obtain a swab as soon as they are able to. (Provided it is on the same day). If this is not until the following day, they will be instructed to document in the diary booklet that a swab wasn't collected, and the reason for not doing so.

Subjects will be given sufficient swabs and courier supplies to enable them to collect the required number of daily swabs. Each subject will receive:

- Swabs,
- Tubes containing the transport medium,
- Spare swabs in case of error,
- Sample biological bags,
- Prepaid/pre-labelled return mail packs,
- Requisition forms;
- Sample labels;
- Torch (for inspection of the genital region);
- Mirror (for inspection of the genital region);
- 'HSV-2 Outbreak' kits for when a subject develops lesions. This kit includes:
  - Swabs;
  - Tubes containing the transport medium,
  - Sample biological bags,
  - Prepaid/pre-labelled return mail packs
  - Requisition Forms; and
  - Sample labels.

Gender specific instructions for obtaining genital swabs will be provided to subjects at Visit 2.

In summary, men will be instructed to obtain the following swabs:

1. Penile skin
2. Perianal and rectal areas.

Women will obtain the following swabs:

1. Vaginal and vulval area;
2. Perianal and rectal areas.

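### The protocol contradicts itself on whether the post-vaccination and post-booster daily swabs are read by viral culture or by PCR, and Section 6.4.9 does not settle it

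*Protocol*

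**What the plan says.** **Baseline period.** The synopsis (Study procedures, Screening/Run in) asks for "once daily swabs of genital secretions for HSV-2 testing for 45 days from Visit 2" and names no method. PCR comes in through eligibility. Section 5.2, criterion 1, requires "positive PCR for HSV-2 during the Baseline Shedding Assessment prior to randomisation". Section 5.3, criterion 8, excludes subjects with a PCR result positive for HSV-1 in the same period. Section 6.3.2.1 has the site check "whether HSV-1 was identified by PCR during the Run-in shedding assessment".

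**Post-vaccination period (from Week 9).** Synopsis, Study Period 1: "subjects will commence collecting post-treatment swabs for viral culture for 45 days".

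**Post-booster period (from Week 25).** Synopsis, Study Period 2: "Subjects will also be required to collect genital swabs for viral culture for 45 days from Week 25". The next sentence reads: "Swabs will be sent to the laboratory for viral load testing, virus typing and/or sequencing".

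**Study-wide assay statement.** Synopsis, Specialised analyses: "PCR analysis for presence and quantification of viral shedding and type". No period is specified.

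**Governing body text.** Section 6.4.9 opens with "Daily genital swabs to detect viral shedding will be performed for 45 days commencing as follows", lists the three periods as one procedure and sends the swabs to the central laboratory. It names no assay. Table 4 in Section 6.4.12 names the laboratory for genital shedding swabs but not the method.

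**Outbreak swabs.** For lesions during the run-in, the synopsis allows either PCR or culture. Under Special protocol requirement / issues, it names only culture for the daily lesion swabs.

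**The concern.** Section 4.2 defines the exploratory efficacy endpoints on the daily swabs as comparisons with baseline: days with detectable shedding after three doses and after the booster, and viral load at the same two stages. Such a comparison needs the same method in each period. Taken literally, the synopsis pairs a PCR baseline with culture in both follow-up periods.

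The culture wording is hard to dismiss as loose shorthand for a swab test. The synopsis itself offers PCR and culture as alternatives for run-in lesion swabs, so it treats them as different methods. It attaches culture to both post-treatment periods and never to the routine run-in swabs.

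Three uses of the data would suffer:

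- **Within-subject change.** A change of method would be inseparable from a change in shedding.
- **The placebo arms.** Section 4.3 gives the description of natural variation in shedding before and after placebo as one of two reasons for including them. A method change would be confounded with that variation.
- **The interim analysis.** Section 11.1.7 plans an unblinded look that includes the shedding data.

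**Working it through.** The protocol gives no figure to reproduce. It states no shedding rate, assay sensitivity or power calculation, and Section 11.1 bases the sample size on practical grounds. The check is therefore a comparison of the text, followed by an illustration.

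**Step 1. What each place implies for the routine daily swabs**

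| Place in the protocol | Baseline | Post-vaccination | Post-booster |
|---|---|---|---|
| Sections 5.2, 5.3 and 6.3.2.1 | PCR | not covered | not covered |
| Synopsis, Study procedures | method not named | culture | culture, then viral load testing |
| Synopsis, Specialised analyses | PCR | PCR | PCR |
| Section 4.2, viral-load endpoints | quantitative assay implied | quantitative assay implied | quantitative assay implied |
| Section 6.4.9 and Table 4 | not named | not named | not named |
| Sections 6.3.2.5 and 6.3.3.3 (Weeks 9 and 25) | not covered | not named | not named |

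The two follow-up columns hold incompatible entries, and no body section decides between them.

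**Step 2. What happens under each reading**

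Let B be the PCR-positive days out of 45 at baseline, with no true change afterwards. Let s be the share of PCR-positive days that culture also detects, and assume culture adds no positive days of its own.

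- PCR in all periods: follow-up count = B, apparent change = 0.
- PCR at baseline, culture afterwards: follow-up count = s × B, apparent relative change = (sB - B)/B = s - 1.

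The documents give neither B nor s. Assume B = 20% of 45 = 9 days:

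| Assumed s | Follow-up days (9 × s) | Apparent change (s - 1) |
|---|---|---|
| 0.9 | 8.1 | -10% |
| 0.6 | 5.4 | -40% |
| 0.3 | 2.7 | -70% |

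The percentage does not depend on B. For viral load, the protocol names no quantity that a culture result would supply for comparison with a PCR baseline.

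**Step 3. Effect on comparison between arms**

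Let r_C and r_P be the true follow-up-to-baseline ratios under COR-1 and placebo. Under mixed assays the observed ratios are s × r_C and s × r_P. If s is the same in every arm, it cancels: (s × r_C)/(s × r_P) = r_C/r_P. The within-arm change is distorted, while the between-arm ratio of relative change is not.

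**The case against.** The strongest reply is that PCR throughout is the evident intention and the culture phrases are careless wording. Much supports this. Specialised analyses names PCR for both presence and quantity. The sentence after the Week 25 culture phrase sends those swabs for viral load testing. Section 6.4.9 treats the three periods as one procedure with one laboratory route, the schedule of assessments uses the same row for all of them, and the visit text for Weeks 9 and 25 does not mention culture. The viral-load endpoints presuppose quantification in every period.

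This stands as far as it goes. A reader might infer that every comparison with baseline will mix two assays. The documents do not support that reading, because it requires two narrative phrases to override the protocol's own assay statement.

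A reader might also infer that a spurious fall would pass for vaccine efficacy. That too goes further than the documents allow. The placebo arms would show the same fall, and Section 11 makes the analysis descriptive. The protection is limited, though: each regimen has 5 placebo subjects (10 in all), pooling them is optional, and the defined endpoints are changes from baseline.

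That culture detects fewer days than PCR is an assumption here, since no section says so. The Study Reference Manual, which was not available, may name the assay, but that would not remove conflicting instructions from the protocol. Likely intent does not settle the matter either: a laboratory or site following the Week 9 sentence would be following the protocol.

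**Conclusion.** The point holds as an internal contradiction about the assay for the post-vaccination and post-booster daily swabs, left unresolved by Section 6.4.9. It creates a risk of mixed assays and does not prescribe them.

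Under the PCR statement in Specialised analyses the artefact is zero. Under the culture wording, the apparent relative change in shedding days with no vaccine effect is s - 1. This rests on an assumed s, on culture adding no positive days, and on s being common to all arms. No single size can be taken from the documents.

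The consequence is confined to exploratory endpoints and to the placebo arms' description of natural variation. The primary safety objective and the secondary immunogenicity objective are unaffected. The point therefore ranks below a must-fix, but it is more than clerical. The assay has to be settled before the swabs are processed, because a later analysis plan cannot supply PCR results for swabs that were only cultured.

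**What to change.** 1. In Section 6.4.9, state that the routine daily swabs in all three 45-day periods are tested by the same quantitative HSV PCR with the same positivity threshold, and that this result alone defines a shedding day and the viral load.
2. In the synopsis, delete the culture phrase from the Week 9 sentence (Study Period 1) and the Week 25 sentence (Study Period 2).
3. Reconcile the two synopsis statements on outbreak swabs. Any culture should be described as additional and should not define a shedding day.

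The cost is a wording amendment. PCR is already the assay named in Specialised analyses, so no new assay, visit or sample is needed. The numerical threshold may sit in the laboratory manual or the statistical analysis plan, provided the protocol states that it is the same in all three periods.
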